### 4.5 Implementation and blinding

Participant recruitment and enrolment will be conducted solely by the PI at the designated OPD. The Medical Officer will implement the randomization by assigning participants to the trial or control group according to the pre-generated block randomization sequence and dispensing the corresponding medication packages. Cognitive Behavioral Therapy (CBT) sessions will be delivered by certified CBT therapists who remain blinded to participant group assignments. A Co-Investigator will be responsible for assessing the outcomes, and they will also remain blinded to the group assignments. The Statistician will be responsible for data analysis and will also remain blinded until the study is complete.

This study employs a double-blind exploratory design to minimize bias. The following personnel will remain blinded throughout the trial:

**Participants:** will be unaware of whether they are receiving *Brahmi* or placebo tablets.**Principal Investigator (PI):** blinded to group allocation to prevent selection and performance biases.**CBT therapists:** administer therapy sessions without knowledge of group assignments to ensure uniformity of intervention delivery.**Co-Investigator:** conducts the outcome assessments while blinded to group allocation.**Statistician:** conducts data analysis blinded to allocation until study completion to reduce analytical bias.**Medical officer:** handles randomization and medication assignment, maintains the confidential coding system, and decodes interventions only after final data analysis or in case of emergency unblinding.

This structured approach ensures rigorous randomization, allocation concealment, and blinding, thereby maintaining methodological integrity and minimizing potential biases throughout the trial.

#### 4.5.1 Emergency unblinding

In emergencies where immediate understanding of the intervention is critical, unblinding may be conducted to prevent harm to the subject. Investigators are urged to consult the Medical Advisor if unblinding is deemed essential.

The Investigator is obligated to uphold the blinding to the greatest extent feasible. The actual allocation must remain confidential from the participant and/or other study personnel, including site personnel or monitors, and there should be no written or verbal disclosure of the code in any related participant papers.

The Investigator is required to document all code violations, along with their justifications, on the relevant CRF page as they arise.

Unblinding should not inherently warrant the cessation of the study drug.

### 4.6 Data collection methods

#### 4.6.1 Pre-screening (demographic data collection)

Before any assessments, participants will fill out a Google Form to provide demographic information and basic eligibility details. The responses will be transcribed into Microsoft Excel for documentation and initial screening purposes.

#### 4.6.2 Initial screening

Participants presenting with PMS symptoms will undergo initial screening using the Premenstrual Symptoms Screening Tool (PSST) and PHQ-9 during a single visit at recruitment (baseline, before Cycle 1). The assessment will be done using paper-pencil in English, and the scores will be recorded in Microsoft Excel.

#### 4.6.3 Pre-intervention observation (screening phase)

During Cycle 1 and Cycle 2, participants will maintain the Daily Record of Severity of Problems (DRSP) daily from Day 1 to the end of the 2nd cycle using paper-pencil in English. A follow-up virtual visit will be conducted on Day 1 or 2 of the 2nd cycle to review progress and clarify doubts. All DRSP scores and notes from the follow-up will be recorded in Microsoft Excel.

#### 4.6.4 Interventional phase

During Cycle 3 and Cycle 4, participants will continue to maintain the DRSP daily from Day 1 to the end of each cycle. Additionally, Sheehan Disability Scale (SDS) and Quality of Life Enjoyment and Satisfaction Questionnaire Short Form (Q-LES-Q-SF) will be assessed on Day 1 or 2 of each cycle using retrospective recall. All scores will be recorded in Microsoft Excel. Assessments will be done using paper-pencil in English.

#### 4.6.5 Documentation

Before enrollment, all participants will be provided with the Informed Consent Form (ICF) and Patient Information Sheet (PIS) in English and Malayalam. Data will be documented using Microsoft Excel with restricted access. Each participant will be assigned a unique study ID code, and no personal identifiers will be included in the main dataset used for analysis. The linkage file containing identifiers will be stored separately under password-protected and encrypted folders accessible only to the Principal Investigator and Co-Investigator. No other trial personnel, including investigators, CBT therapists or Statistician will have access to this master file; they will only handle anonymized case-record forms relevant to their role. Regular backups will be maintained on secure institutional servers to ensure the data integrity. The role-based restricted access ensures confidentiality, prevents unauthorized viewing. These documents will be maintained in paper form, with a digital log as needed.

Table 2 presents the schedule of assessments, detailing the tools, timing, methods, and data recording procedures across the pre-screening, screening, and interventional phases of the study.

**TABLE 2 T2:** Schedule of assessments and data collection methods.

Phase	Assessment tool	Days of assessment	Method	Language	Timeline	Data recording
Pre- screening	Google form (demographics, eligibility)	Before enrollment	Digital → transcribed to Excel	English	Baseline, before Cycle 1	Responses recorded in Microsoft Excel
Initial screening	PSST, PHQ-9	Single visit at recruitment	Paper-pencil	English	Baseline, before Cycle 1	Scores recorded in Microsoft Excel
Pre-intervention observation (screening phase)	Daily Record of Severity of Problems (DRSP)	Daily, Day 1 to end of 2nd cycle	Paper-pencil	English	Cycle 1 and Cycle 2 (screening)	Scores recorded in Microsoft Excel
Pre-intervention observation (screening phase)	Follow-up virtual visit	Day 1 or 2 of 2nd cycle	Virtual	English	After completion of Cycle 2 DRSP	Notes recorded in Microsoft Excel
Interventional phase	Daily Record of Severity of Problems (DRSP)	Daily, Day 1 to end of each cycle	Paper-pencil	English	Cycle 3 and Cycle 4 (intervention)	Scores recorded in Microsoft Excel
Interventional phase	Sheehan Disability Scale (SDS), Q-LES-Q-SF	Day 1 or 2 of each cycle (retrospective recall)	Paper-pencil	English	Cycle 3 and Cycle 4, retrospective assessment of previous cycle	Scores recorded in Microsoft Excel
Documentation	Informed Consent Form (ICF), Patient Information Sheet (PIS)	Before enrollment	Paper	English & Malayalam	Baseline, before Cycle 1	Digital log maintained

#### 4.6.6 Retention

This study informs participants that their involvement is completely voluntary, and they may quit at any time without repercussions. If a participant opts to withdraw for any reason, their decision will be acknowledged. Efforts shall be undertaken to prevent unnecessary dropouts, where feasible. Participants who choose to withdraw will not be subject to any additional data collection or follow-up. This methodology guarantees compliance with ethical norms, honoring participants’ autonomy and rights during the research process.

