#### 4.2.2 Sample size

The proposed study is a randomized controlled exploratory trial aimed at providing preliminary insights into the comparative outcomes of two independent groups. As formal power calculations are not mandatory for exploratory studies, a two-sample t-test formula for comparing means was applied primarily to provide a rational basis for determining a feasible sample size:

$$n=\frac{2\,s_{p}^{2}\,{\left[Z_{1-\alpha /2}+Z_{1-\beta }\right]}^{2}}{\mu_{d}^{2}}$$

This formula incorporates the pooled variance, the anticipated mean difference between groups, the significance level (α), and statistical power (1−β). Using estimates from published data, the pooled variance (sp^2^) was taken as 2.85, and the expected mean difference (μd) between groups as 1.83. For reference, a two-sided test with a significance level of 0.05 (Z = 1.96) and a nominal power of 90% (Z = 1.28) was considered. Substituting these values yielded a preliminary estimate of approximately 18 participants per group. Allowing for an anticipated dropout rate of 20%, the adjusted number was approximately 23 participants per group, resulting in a total sample size of 46.

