### 4.10 Safety

All adverse events (AEs) and serious adverse events (SAEs) will be systematically documented in the Case Report Form (CRF) using a predefined Adverse Drug Reaction (ADR) page. Each entry will capture the event description, diagnosis (if available), onset and resolution dates, severity (mild, moderate, or severe), action taken with the study drug (none, temporarily interrupted, or permanently withdrawn), outcome (resolved, resolved with sequelae, or not resolved), and the assessed relationship to the study drug (definite, probable, possible, unlikely, not related, or not assessable). The Principal Investigator and Co-Investigator will independently evaluate causality, taking into account the temporal relationship with the study drug, the participant’s clinical course, medical history, and concomitant medications. All adverse events will be followed until resolution or stabilization. Events occurring after a participant exits the study will not be routinely reported unless the investigators consider a reasonable likelihood of relation to the study drug, psychotherapy, or study procedures. This systematic documentation ensures continuous monitoring and prioritization of participant safety throughout the trial

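### Sections 4.6.6 and 4.10 contradict each other on adverse events still open when a participant withdraws, so it is undefined whether their final outcome is collected

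*Protocol article*

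**What the plan says.** Section 4.6.6 (Retention) covers leaving the study for whatever cause: "If a participant opts to withdraw for any reason, their decision will be acknowledged". It then states the rule on data: "Participants who choose to withdraw will not be subject to any additional data collection or follow-up". The reason it gives is respect for participants' autonomy.

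Section 4.10 (Safety) states: "All adverse events will be followed until resolution or stabilization". It adds: "Events occurring after a participant exits the study will not be routinely reported", with an exception where the investigators judge a link to the tablets, the psychotherapy or the trial procedures reasonably likely. The adverse event page of the case report form records onset and resolution dates, severity, causality, the action taken with the study drug (permanent withdrawal of the drug is one option) and the outcome (not resolved is one option).

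Section 3.1 (Trial design) names safety among the things the trial is meant to observe, and Section 6 (Limitations) says that exploratory designs mainly inform on feasibility and safety. Section 4.2.2 (Sample size) plans for 20% dropout.

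**The concern.** Both rules are absolute and neither refers to the other. Section 4.6.6 ends collection for anyone who chooses to withdraw, which includes a woman who leaves because of an adverse event. Section 4.10 requires that same event to be followed to its end. Site staff cannot comply with both.

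The information at risk is how events end among women who leave the study. Section 3.10 foresees nausea, vomiting, diarrhoea, cramps, insomnia and heightened anxiety, any of which could lead a participant to leave. With 23 women per arm, a few truncated event records matter to a description of tolerability. If staff resolve the conflict differently from case to case, the records will also not be comparable. There is a duty to the participant as well: Section 4.10 promises follow-up that Section 4.6.6 takes away.

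**Working it through.** **Step 1: the two rules for one case.** Take a woman who withdraws by choice while an adverse event is still open.

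- Under Section 4.6.6, no further data are collected and she is not followed.
- Under Section 4.10, the event is followed until it resolves or stabilises, and its resolution date and outcome are entered.
- No sentence ranks the two sections or makes an exception in either. A fuller protocol could not make both true as written, because one of them has to be qualified. This is a contradiction in what is stated, not a detail left out of a condensed article.

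**Step 2: events that begin after exit.** Section 4.10 allows reporting when the investigators think a relation reasonably likely. For women who withdrew, Section 4.6.6 ends the planned follow-up through which the investigators would learn of such an event, and it does not say whether one that comes to light may be recorded.

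**Step 3: what is undefined, and what is not.**

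- Resolved before withdrawal: the outcome is already on the form and is not affected.
- Open at withdrawal: occurrence, onset, severity and causality can be on the form, and the outcome can be entered as not resolved. Whether the final outcome is ever sought is undefined.

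**Step 4: an upper bound on the number.** The inputs come from Section 4.2.2: pooled variance 2.85, difference 1.83, Z values 1.96 and 1.28, dropout 20%.

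- The plan's own figure: n = 2 × 2.85 × (1.96 + 1.28)² / 1.83² = 17.87, so 18 per group. Then 18 / (1 − 0.20) = 22.5, so 23 per group and 46 in total. The stated figures reproduce and are not in dispute.
- Anticipated dropout: 46 × 0.20 = 9.2, about 9 women. This includes loss to contact and withdrawals with no open event, so it is a ceiling.

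The document does not give the share s of dropouts who withdraw with an event open. Taking s as an assumption, and women as independent, the expected number is 9.2 × s and the chance of at least one is 1 − (1 − 0.20 × s)^46:

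| Assumed s | Expected women | Chance of at least one |
|---|---|---|
| 10% | 0.9 | 61% |
| 25% | 2.3 | 91% |
| 50% | 4.6 | 99% |

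Over this range the case is more likely than not to arise at least once, but it concerns few women.

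**The case against.** The best defence is that Section 4.10 is the specific safety rule, while Section 4.6.6 is a retention paragraph within the data collection methods, so the specific rule should be read as prevailing. The provision in Section 4.10 for related events after exit suggests that safety reporting was meant to reach beyond departure. Section 3.9.6 also encourages participants to contact the centre about side effects, and contact that a woman starts herself is compatible with her not being followed up. This is a reasonable guess at the intention, but the text does not state it. Section 3.9.6 does not expressly extend to women who have left.

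The defence does defeat three stronger readings.

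- A reader might infer that women who leave because of an adverse event have no recorded outcome. That assumes Section 4.6.6 overrides Section 4.10, which no sentence says. Even if it did, the form allows an outcome of not resolved.
- A reader might infer that tolerability would look better than it was. An event documented before withdrawal still counts in its arm, and an entry of not resolved looks worse, not better. What could be lost is later resolution, or an event that was never disclosed.
- A reader might infer that stopping tablets ends all follow-up. The form records stopping the drug as an action on treatment, and Section 3.8 treats women below the adherence thresholds as partial adherents whose status feeds a sensitivity analysis. Nothing says that stopping tablets or CBT triggers Section 4.6.6. Nothing rules it out either, so a clarifying sentence is useful.

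The short interval between a completer's last tablet and the final contact is a separate matter. Completers are outside this conflict, and Section 4.10 follows their known events in any case.

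**Conclusion.** The contradiction stands, limited to adverse events open at withdrawal and, less sharply, to related events arising afterwards in women who withdrew. It is undefined whether the final outcome of the former is collected. The documents do not support saying that it will be missing.

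The size is small and unknown: a fraction of the anticipated 20% dropout. The shares in the table are assumptions. No sample size figure depends on this point. It still deserves correction, because safety is one of the few things that a trial of this size sets out to describe and because the two instructions cannot both be followed.

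**What to change.** Reconcile the two sections as follows.

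1. Limit the rule in Section 4.6.6 to women who withdraw consent to further contact. State that stopping tablets or CBT alone does not end the diary, the questionnaires or the final online contact.
2. State that adverse events open at withdrawal are followed under Section 4.10 unless the woman declines, in which case her status at last contact is recorded.
3. Align the sentence in Section 4.10 on events after exit, so that it is clear whom it covers and how such events may be reported for women who withdrew.

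These changes concern data collection only and set no treatment rule. The cost is a few sentences in the protocol, matching consent wording, and brief further contact with a few women, who keep the right to refuse. A side benefit is fuller outcome data for the intention-to-treat analysis in Section 4.9, whose primary handling of missing data is complete-case.

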#### 4.6.7 Data management

Data entry and documentation will be performed both manually, using paper-pencil forms completed by participants, and electronically, using Microsoft Excel. The Principal Investigator (PI) will oversee the process, ensuring the accuracy and completeness of all data and providing clarification to participants if needed. The Co-Investigator will be responsible for entering scores from the paper forms, outcome assessments, and follow-up notes into Excel, maintaining blinding where applicable. All participant data will be organized numerically by participant ID and stored in a secure location to ensure confidentiality while allowing authorized access for study personnel. Only validated scores and documented observations will be included in the analysis. The Statistician, who remains blinded to group allocation, will perform all analyses according to the study protocol, comparing outcomes between the Trial (CBT + *Brahmi*) and Control (CBT + Placebo) groups. Participant confidentiality will be rigorously maintained throughout the study, and all records will be retained for a minimum of 5 years following study completion to allow for verification, audit, or future reference.

### 4.7 Exploratory statistical analysis

Exploratory statistical analysis will primarily explore the potential impact of Cognitive Behavioral Therapy (CBT) combined with either *Brahmi* (Bacopa monnieri) tablets or placebo in participants with moderate to severe Premenstrual Syndrome (PMS). Outcome measures include the Daily Record of Severity of Problems (DRSP), Quality of Life Enjoyment and Satisfaction Questionnaire (Q-LES-Q), and Sheehan Disability Scale (SDS), assessed at three time points: baseline (third visit), during treatment (fourth visit), and post-treatment (fifth cycle follow-up). Analyses will be descriptive, focusing on effect size estimates and 95% confidence intervals to provide insights into the direction and magnitude of observed effects. P values will be presented descriptively without inferential claims, in line with the exploratory nature of the study. Where appropriate, repeated measures approaches such as ANOVA or mixed-effects models may be applied to summarize changes over time and between groups, with emphasis placed on effect size interpretation to generate preliminary signals for future confirmatory research.

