## Abstract

Premenstrual syndrome (PMS) is a widespread and under-recognized disorder, characterized by cyclical recurrence of physical, psychological, and behavioral symptoms during the luteal phase, significantly impacting the daily functioning of women. Cognitive Behavioral Therapy (CBT) is an established non-pharmacological strategy for PMS, while *Brahmi* (Bacopa monnieri), a classical Ayurvedic herb, has traditionally been used to enhance cognition, reduce anxiety, and support emotional balance. This exploratory study evaluates whether combining *Brahmi* with CBT offers additional benefit compared to CBT alone. It is a double-blind, randomized, placebo-controlled exploratory clinical trial (CTRI/2025/02/081239) conducted at the Amrita School of Ayurveda, Kollam, Kerala, with sponsorship from the Central Council for Research in Ayurveda Sciences (CCRAS). Forty-six women aged 18–24 years, diagnosed with moderate to severe PMS using the Premenstrual Symptoms Screening Tool (PSST) and the Daily Record of Severity of Problems (DRSP), will be recruited and randomly assigned to receive either CBT with *Brahmi* tablets or CBT with placebo tablets. The primary outcomes include reduction in PMS severity, assessed by DRSP, and improvement in quality of life measured with the Quality of Life Enjoyment and Satisfaction Questionnaire (Q-LES-Q SF). Secondary outcome is reduction in functional disability measured using the Sheehan Disability Scale. Assessments will be conducted at baseline, during treatment, and at follow-up. Statistical analysis will be carried out using repeated measures ANOVA with Bonferroni-adjusted post hoc tests, significance set at *p* < 0.05, and effect sizes reported. A limitation of this design is that it cannot disentangle the individual effects of *Brahmi* from CBT, allowing conclusions only on the combined intervention. The study aims to generate preliminary exploratory evidence for a safe, integrative, and accessible approach to PMS management in young women.

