## 4 Outcome measures

### 4.1 Exploratory primary outcomes

• Changes in PMS symptom severity, as measured by the Daily Record of Severity of Problems (DRSP) across two intervention cycles.

• Changes in quality of life, as assessed by the Quality-of-Life Enjoyment and Satisfaction Questionnaire Short Form (Q-LES-Q SF 12) from baseline to post-intervention.

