#### 4.2.1 Participant timeline

Participants enrolled in the study will undergo a structured series of visits spanning multiple menstrual cycles. During the first visit, personal history, socio-demographic information, and detailed menstrual history will be recorded. Participants will also complete the Patient Health Questionnaire-9 (PHQ-9) to assess depressive symptoms and the Premenstrual Symptoms Screening Tool (PSST) to evaluate the presence and severity of PMS. Individuals who meet the criteria for moderate to severe PMS based on the PSST will be considered eligible for further participation. At this stage, informed consent will be obtained. During the second visit, which occurs on the 1st or 2nd day of the subsequent menstrual cycle, the screening process will begin. This is followed by an initial Google Meet session at the same phase of the following cycle to confirm ongoing eligibility and provide further study orientation. The third visit (baseline) will be on 1st to 2nd day of the participant’s menstrual cycle, during which assessments using the Daily Record of Severity of Problems (DRSP), Quality of Life Enjoyment and Satisfaction Questionnaire (Q-LES-Q), and Sheehan Disability Scale (SDS) will be conducted. The intervention begins at the fourth visit (aligned with the 1st to 2nd day of the second menstrual cycle), where participants will be randomly assigned to receive either Cognitive Behavioral Therapy (CBT) combined with *Brahmi* tablets (interventional group) or CBT with placebo tablets (comparator group). CBT sessions will be given on the 5*^th^*, 12*^th^*, 19*^th^* and 26*^th^* day for 2 menstrual cycles with total of eight sessions. A final Google Meet follow-up will be conducted during the 1st to 2nd day of the fifth menstrual cycle to assess outcomes and gather participant feedback.

The schedule of visit chart is mentioned in Table 1. It explains the follow-up visits across four menstrual cycles during the study.

**TABLE 1 T1:** Schedule of visit chart.

Activity/assessment	1^st^ visit (history taking, PSST assessment)	2^nd^ visit (start screening 1^st^ to 2^nd^ day menstrual cycle)	G Meet (1^st^ to 2^nd^ day of next menstrual cycle)	3^rd^ visit Baseline visit (1^st^ to 2^nd^ day of menstrual cycle)	4^th^ visit (1^st^ to 2^nd^ day of 2^nd^ menstrual cycle)	G Meet (1^st^ to 2^nd^ day of 5^th^ menstrual cycle)
Personal history, socio-demographic data, and menstrual history						

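### The DRSP primary endpoint is internally inconsistent: the analysis time points are Day 1-2 visits, while the outcome, the diary and the definition of PMS point to other days and cycles

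*Protocol article*

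**What the plan says.** All references are to the protocol article.

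- Section 4.7 has the DRSP, Q-LES-Q and SDS assessed three times: "baseline (third visit), during treatment (fourth visit), and post-treatment (fifth cycle follow-up".
- Section 4.2.1 says that the third (baseline) visit "will be on 1st to 2nd day of the participant’s menstrual cycle, during which assessments using the Daily Record of Severity of Problems (DRSP" are made, together with the other two scales. The fourth visit is "aligned with the 1st to 2nd day of the second menstrual cycle", and it is there that randomisation takes place and the intervention begins. The final online contact is on Day 1-2 of the fifth cycle.
- Section 4.1 gives the first primary outcome as change in symptom severity "as measured by the Daily Record of Severity of Problems (DRSP) across two intervention cycles".
- Section 4.6.3 says that in Cycles 1 and 2 "participants will maintain the Daily Record of Severity of Problems (DRSP) daily from Day 1 to the end of the 2nd cycle". Section 4.6.4 continues the daily diary through Cycles 3 and 4, the interventional phase. Table 2 repeats this and schedules no DRSP diary in Cycle 5.
- The Abstract characterises PMS by "cyclical recurrence of physical, psychological, and behavioral symptoms during the luteal phase". Section 2.1.3 justifies the DRSP by its prospective daily format.

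**The concern.** These statements do not describe one endpoint. Section 4.7 names visits held as bleeding starts. Section 4.1 names a span of two treated cycles. The disorder is defined by the days before bleeding.

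A score taken at the visits would mix menstrual complaints with premenstrual symptoms that are already remitting. It would also fall on days when, under section 3.4, tablets are withheld in both arms. A benefit confined to the premenstrual days could then be missed.

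The time labels are a separate problem. A value taken when treatment starts cannot show an effect of treatment, whatever days it summarises. Section 4.7 makes effect sizes and 95% confidence intervals the product of the trial, so which days and cycles enter them decides what the trial reports. If this stays open, the window can be chosen after the data are seen.

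**Working it through.** **1. The plan's only related figure.** Section 4.2.2 gives a pooled variance of 2.85, a difference of 1.83, Z values of 1.96 and 1.28, and 20% dropout. Then n = 2 × 2.85 × (1.96 + 1.28)² / 1.83² = 17.87, rounded up to 18 per group. 18 / 0.80 = 22.5, rounded up to 23, and 46 in total. The stated figures reproduce. The section does not say that 2.85 and 1.83 refer to the DRSP, to one day or to a mean over days, so no loss of planned power can be derived from them.

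**2. The three time points under the two possible readings.** The right-hand column assumes that the visits open Cycles 3, 4 and 5 in the numbering of sections 4.6.3-4.6.4.

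| Label in 4.7 | Timing in 4.2.1 | Rating made on the visit day | Visit closes the previous cycle's diary |
|---|---|---|---|
| Baseline | Third visit, Day 1-2 | Menstrual-day score, untreated | Cycle 2, untreated |
| During treatment | Fourth visit, Day 1-2; randomisation and start of intervention | Menstrual-day score as treatment starts | Cycle 3: treated by 4.6.4, untreated by 4.2.1 |
| Post-treatment | Day 1-2 of fifth cycle | Menstrual-day score; no Cycle 5 diary scheduled | Cycle 4, treated |

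On the first reading, two of the three time points carry no treatment effect, the third has no scheduled diary behind it, and none falls in the luteal phase. The second reading fits the labels in 4.7 and the outcome in 4.1, but only if the fourth visit is not where the intervention begins, which is what 4.2.1 says it is. Section 4.2.1 also calls the fourth-visit cycle the second one, while 4.6.4 opens the interventional phase with Cycle 3. The article gives no counting convention that links the two.

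**3. Which diary days.** Even on the second reading, no section restricts the score to premenstrual days. As an illustration, suppose that an effect is confined to 7 premenstrual days. Eligibility requires cycles of 25-35 days (section 3.3.1), so a whole-cycle mean would carry 7/35 = 20% to 7/25 = 28% of that difference.

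**4. Precision, as an illustration only.** The variance of a k-day mean relative to one day is (1 + (k − 1)ρ) / k, where ρ is the correlation between days. Neither ρ nor k is in the article. Assumed here: ρ from 0.3 to 0.9 and k of 5 or 7.

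| ρ | k = 5 | k = 7 |
|---|---|---|
| 0.3 | 2.2/5 = 0.44 | 2.8/7 = 0.40 |
| 0.5 | 3.0/5 = 0.60 | 4.0/7 = 0.57 |
| 0.7 | 3.8/5 = 0.76 | 5.2/7 = 0.74 |
| 0.9 | 4.6/5 = 0.92 | 6.4/7 = 0.91 |

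The variance falls by between 1 − 0.92 = 8% and 1 − 0.40 = 60%. In standard errors that is 1 − √0.92 = 4% to 1 − √0.40 = 37%. The gain arises only if single-day scores would otherwise be analysed.

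**The case against.** The strongest reply is that section 4.7 names visits, not the days that are scored. The DRSP is described throughout as a daily diary, and Day 1-2 of a cycle is a natural moment to collect the diary of the cycle just ended. Table 2 uses this logic for the SDS and Q-LES-Q-SF, which look back at the previous cycle. The fifth-cycle contact would then close the Cycle 4 diary, so no Cycle 5 diary would be needed.

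Much of this stands. A reader might infer that the endpoint does measure the wrong days. The documents do not support that, because no section says that only Day 1-2 ratings are scored. A reader might also claim a definite gain in precision, but the correlation is unknown and the plan never specifies the single-day comparator.

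The reply does not remove the inconsistency. The look-back is stated for the SDS and Q-LES-Q-SF and not for the DRSP, while section 4.2.1 lists DRSP assessment among the procedures of the Day 1-2 baseline visit. The conflict over the fourth visit remains on either reading.

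A second reply is that a condensed article may leave scoring rules to an analysis plan that is not shown. That is fair for the averaging window and the handling of missing days. It does not cover time points that the article itself fixes and that disagree with its own outcome and schedule. Section 4.6.7 has the statistician analyse according to the protocol, so the conflict would carry over.

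A third is that the trial is exploratory and its P values descriptive. This limits what will be claimed, but the effect estimate still has to refer to known days and cycles.

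**Conclusion.** The point holds as an inconsistency in the definition of a primary endpoint. Sections 4.1, 4.2.1, 4.6.3-4.6.4 and 4.7 cannot all be followed. Taken literally, 4.2.1 and 4.7 give menstrual-day scores and a mislabelled middle time point. Taken charitably, they leave the days scored unstated for the DRSP, and the fourth-visit label still conflicts with the start of the intervention.

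The finding that the passages conflict rests on the text alone and needs no assumption. Its numerical effect is not known: the 8-60% variance range depends on the assumed correlation and window and on single-day scoring, and the 20-28% dilution depends on an effect confined to 7 days. The stated sample size is unaffected. The daily data are collected on either reading, so nothing is lost if the definition is settled before allocation is revealed.

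**What to change.** Reconcile sections 4.1, 4.2.1, 4.6.4 and 4.7:

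- Define the DRSP score per cycle as the mean daily total over a pre-specified premenstrual window from the existing diary, for example the last 7 days before the next menses, with a minimum number of completed days.
- Use the pre-randomisation screening cycles (1 and 2) as baseline and the treated cycles (3 and 4) as outcome.
- Estimate the difference between arms, adjusted for that baseline, with a 95% CI.
- Stop using Day 1-2 visit values as DRSP time points. The visits can remain the occasions for collecting the diary.
- State one cycle numbering, and reconcile the fourth visit's label in 4.7 with the start of the intervention in 4.2.1 and 4.6.4.

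Whether Cycle 4 alone or both treated cycles form the primary comparison is for the sponsor to decide, provided it is pre-specified and agrees with section 4.1.

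The cost is small. No new data are needed, but a minimum-days rule has to be set. Because the trial is registered and ethics-approved, the endpoint wording has to be amended formally.
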